##### PLEASE ATTACH A COPY OF THE PLAIN LANGUAGE STATEMENT TO YOUR APPLICATION

Please see Appendix G for the Plain Language Statement.

#### 4.3 OBTAINING CONSENT

(a) How will each participant's consent be established?

By signing and returning a Consent Form – see 4.4 below

☐

By returning an anonymous survey

☐

Via a verbal agreement

☐

Via a person with lawful authority to consent (eg. parent, doctor) – see 4.3(b) below

☐

Via a recorded agreement for interview

☐

**Other** (Please describe in no more than 50 words):  
Participants will select a tick box online indicating their informed consent to participate. This consent will be stored in the data file. "I have read the information sheet for this study and agree to participate under the conditions described. YES/NO"

☒

(b) If participants are unable to give informed consent, explain who will consent on their behalf and how such consent will be obtained.

If participants are unable to give informed consent they will not be eligible to participate.

#### 4.4 CONSENT FORM (IF APPLICABLE)

(N/A)

##### CONFIRM THAT THE CONSENT FORM WILL:

|                                                                                                                                                                                          | YES                      | NOT APPLICABLE           |
|------------------------------------------------------------------------------------------------------------------------------------------------------------------------------------------|--------------------------|--------------------------|
| 1. be printed on University of Melbourne letterhead                                                                                                                                      |  |                          |
| 2. include the title of the project and names of researchers                                                                                                                             |  |                          |
| 3. state that the project is for research purposes                                                                                                                                       |  |                          |
| 4. state that involvement in the project is voluntary and that participants are free to withdraw at any time, and free to withdraw any unprocessed identifiable data previously supplied |  |                          |
| 5. outline particular requirements of participants including, for example, whether interviews are to be audio and/or video-taped                                                         |  |  |
| 6. include arrangements to protect the confidentiality of data                                                                                                                           |  |                          |
| 7. include advice that there are legal limitations to data confidentiality (see below)**                                                                                                 |  |                          |
| 8. (if the sample size is small) confirm that this may have implications for protecting the identity of the participants                                                                 |  |  |
| 9. (once signed and returned) be retained by the researcher                                                                                                                              |  |                          |

[\*\*Re 7 – it is possible for data to be subject to subpoena, freedom of information request or mandated reporting by some professions. Depending on the research proposal you may need to specifically state and explain these limitations]

##### PLEASE ATTACH A COPY OF THE CONSENT FORM TO YOUR APPLICATION

#### 5. PRIVACY AND CONFIDENTIALITY

Privacy can be described as "...a complex concept that stems from a core idea that individuals have a sphere of life from which they should be able to exclude any intrusion." A major application of the concept of privacy is information privacy: the interest of a person in controlling access to and use of any information personal to that person. 'Confidentiality', a narrower more specific term than 'privacy' refers to the legal and ethical obligation that arises from a relationship in which a person receives information from or about another.

At the Commonwealth level, the collection, storage, use and disclosure of personal information by Commonwealth agencies is regulated by the *Privacy Act 1988*. Sections 95 and 95A of the Act are of particular relevance to researchers. There is regulation at State and Territory level in the form of legislation related to privacy generally or the administration of agencies, or administrative codes of practice. In Victoria, the *Health Records Act 2001* regulates health information handled by the Victorian public sector and private sector, while the *Information Privacy Act 2000* regulates the collection and handling of non-health-related personal information. The National Statement states that an HREC must be satisfied that a research proposal conforms to all relevant Commonwealth, State or Territory privacy legislation or codes of practice]

##### 5.1 ACCESSING PERSONAL INFORMATION

[Personal Information' includes names, addresses, or information/opinion about an individual whose identity is apparent, or can reasonably be ascertained, from the information/opinion. It also includes Health Information (e.g. health opinions, organ donation or genetic information) and Sensitive Information (e.g. political views, sexual preferences, criminal records)]

Is there a requirement for the researchers to obtain **Personal Information** (either identifiable or potentially

identifiable) about individuals **without their consent**?

- |                                                                    | YES                      | NO                                  |
|--------------------------------------------------------------------|--------------------------|-------------------------------------|
| a) from Commonwealth departments or agencies?                      |  |  |
| b) from State departments or agencies?                             |  |  |
| c) from Other Third Parties, such as non-government organisations? |  |  |

If you answered YES to (a), (b) or (c), you will need to complete [Module P](#) and attach it to this application

## 5.2 REPORTING PROJECT OUTCOMES

(a) Will the project outcomes be made public at the end of the project?

- ☒ YES ☐ NO

(If YES, give details of how the results will be made public (eg in journal articles book, conference paper, the media, working paper or other). If NO, explain why not.

The findings will be disseminated to researchers and health professionals in journals and at conferences. An effort will be made to disseminate the findings to the public through the media.

(b) Will a report of the project outcomes be made available to participants at the end of the project?

- ☒ YES ☐ NO

(If Yes, give details of the type of report and how it will be made available. If No, explain why not.

A report of the project outcomes will be made available on the website.

## 5.3 WILL THE RESEARCH INVOLVE:

- |                                                                                                                                                                                                                                                                                                                                                  | YES                                 | NO                                  |
|--------------------------------------------------------------------------------------------------------------------------------------------------------------------------------------------------------------------------------------------------------------------------------------------------------------------------------------------------|-------------------------------------|-------------------------------------|
| • complete anonymity of participants (i.e., researchers will not know the identity of participants as participants are part of a random sample and are required to return responses with no form of personal identification)?                                                                                                                    |             |  |
| • de-identified samples or data (i.e., an irreversible process whereby identifiers are removed from data and replaced by a code, with no record retained of how the code relates to the identifiers. It is then impossible to identify the individual to whom the sample of information relates)?                                                |             |  |
| • potentially identifiable samples or data (i.e., a reversible process in which the identifiers are removed and replaced by a code. Those handling the data subsequently do so using the code. If necessary, it is possible to link the code to the original identifiers and identify the individual to whom the sample or information relates)? |  |             |
| • participants having the option of being identified in any publication arising from the research?                                                                                                                                                                                                                                               |             |  |
| • participants being referred to by pseudonym in any publication arising from the research?                                                                                                                                                                                                                                                      |             |  |
| • any other method of protecting the privacy of participants? Please describe:                                                                                                                                                                                                                                                            |                                     |                                     |

Note that where the sample size is very small, it may be impossible to guarantee anonymity/confidentiality of participant identity. Participants involved in such projects need to be clearly advised of this limitation in the Plain Language Statement.

## 6. DATA STORAGE, SECURITY AND DISPOSAL

### 6.1 DATA STORAGE

Does data storage comply with the University policy? [University of Melbourne Policy on the Management of Research Data and Records is available at: <http://www.unimelb.edu.au/records/research.html> The Joint NHMRC/AVCC Statement and Guidelines on Research Practice is available at: <http://www.nhmrc.gov.au/funding/policy/researchprac.htm> ]

☒ YES ☐ NO (If NO, please explain.)

### 6.2 DATA SECURITY

(a) Will the Principal Researcher be responsible for security of data collected?

☒ YES ☐ NO (If NO, please provide further details. You may also use this space to explain any differences between arrangements in the field, and on return to campus.)

(b) Will data be kept in locked facilities in the Department through which the project is being conducted?

☒ YES ☐ NO (If NO, please explain how and where data will be held, including any arrangements for data security during fieldwork.)

(c) Which of the following methods will be used to ensure confidentiality of data?  
(select all options that are relevant)

- data and codes and all identifying information to be kept in separate locked filing cabinets ☒
- access to computer files to be available by password only ☒
- access by named researcher(s) only ☒
- other (please describe) ☐

(d) Will others besides the researchers associated with this project have access to the raw data?

☐ YES ☒ NO (If YES, please explain who and for what purpose? What is their connection to the project?)

### 6.3 DATA RETENTION AND DISPOSAL

[Research data and records should be maintained for as long as they are of *continuing value* to the researcher and as long as recordkeeping requirements such as patent requirements, legislative and other regulatory requirements exist. The minimum retention period for research data and records is five years after publication, or public release, of the work of the research as stated in the University of Melbourne [Code of Conduct for Research](#). If the project involves clinical trial(s), the data should be kept for a minimum of 15 years (refer to Section 3.3 of the National Statement for further details)]

*Specify how long materials (e.g. files, audiotapes, questionnaires, videotapes, photographs) collected during the study will be retained after the study and how they will ultimately be disposed of.*

A data file will be kept for at least 5 years after publication or as long as interest in the data continues.

## 7. POTENTIAL CONFLICT OF INTEREST

### 7.1 POTENTIAL CONFLICT OF INTEREST

Is there any affiliation or financial interest for researchers in this research or its outcomes or any circumstances which might represent a perceived, potential or actual conflict of interest?

☐ YES ☒ NO (If YES, give brief details?)

[If you have declared a potential conflict of interest, you should include an appropriate comment on the Plain Language Statement and Consent Form]

## 7.2 COMPLIANCE WITH THE CODE OF CONDUCT FOR RESEARCH

[University researchers must disclose and manage Conflict of Interest in accord with the provisions of the University's Code of Conduct for Research. See <http://www.unimelb.edu.au/ExecServ/Statutes/r171r8.html> ]

Is the Conflict of Interest noted above in section 7.1 being managed in accordance with the Code of Conduct?

☐ YES ☐ NO ☒ Not Applicable

## 11. WHEN COMPLETE

**When this form has been completed and finalised it should be attached to the coversheet section of the application completed in Themis Research and then submitted to the nominated Human Ethics Advisory Group for review.**

THE UNIVERSITY OF MELBOURNE  
HUMAN RESEARCH ETHICS COMMITTEE

REQUEST FOR AMENDMENT

2. PROJECT DETAILS

Title: Promotion of self-help strategies for sub-threshold depression: An e-mental health RCT

Brief Description: Depressive symptoms are common, impair individual functioning, and may develop into major depression. Self-help strategies, such as exercise or taking time off work, are well-liked and often used by those with depressive symptoms. However, some strategies are not as effective as others, and some may be harmful (e.g. substance use). Previous research has identified a set of helpful and feasible self-help strategies. This project will test the feasibility of promoting these strategies via email messages to individuals with a high level of depressive symptoms. The aim is to reduce the overall level of depressive symptoms as well as the number of individuals developing major depression.

Project Approval Period: From: 04-Jun-2009 To: 31-Dec-2011

## 4. REQUEST FOR AMENDMENT DETAILS

### 4.1 Nature of and reason for amendment

We propose three amendments to the project.

1) We wish to amend the inclusion criteria of the project, to allow participation from anyone interested in the study regardless of their depression status (phase two). Previously, participation was restricted to adults with sub-threshold symptoms of depression, who were not receiving depression treatment (phase one). We would like to open up the study to those with full threshold depression, as well as those with any number of symptoms. Undergoing concurrent treatment for depression will also not be an exclusion criterion, because the intervention does not interfere with psychological or medical treatment. This recognizes that participants will be more likely to be in treatment if they have full-threshold depression.

We wish to make this amendment because preliminary analyses of the study show that the Mood Memo emails change self-help coping behaviour, and depressive symptoms to a smaller extent. We hypothesise that the effect on depressive symptoms will be greater for those who are more depressed at the beginning of the study than for those with sub-threshold depression. We think this is probable because effect sizes are typically greater for treatment studies than for prevention studies (Jané-Llopis, Hosman, et al., 2003). Furthermore, there was significant interest in participating from individuals who were already in treatment or who had 'full' depression, and it would be worthwhile investigating whether the Mood Memos had any effects additional to treatment effects.

We plan to analyse the data collected with the changed inclusion/exclusion criteria separately from that already collected in phase one. This is feasible because of the number of participants recruited to date. This will also preclude any suggestion that the trial is being extended to ‘chase’ statistical significance.

We will continue to advertise the study and recruit participants in the same manner as before (primarily through Google advertising). We will aim for a sample size of 1600 participants in this second phase of the study. This is based on a power analysis indicating that a sample of 393 per condition would give 80% power to detect a small effect size (0.2 standard deviations between conditions) on a continuous outcome measure assuming a correlation of 0.5 between pre- and post-test scores. As approximately 50% of participants in phase one did not complete the post-test assessment, a total sample of 1600 allows for a similar rate of attrition. 1600 participants is a feasible target given that 1336 participants with sub-threshold depression were recruited in phase one.

To clarify, the inclusion criteria will now be:

- a. 18 years or older
- b. Access to the internet at least once per week
- c. Resident of Australia, New Zealand, Canada, Ireland, United Kingdom, USA
- d. Any score on the PHQ-9 depression questionnaire
- e. Informed consent

2) The second change we propose is to send an additional reminder email requesting the participant to complete post- and follow-up assessments, bringing the number of reminders to two. This is because up to 50% of participants did not complete assessments, and the reminder email resulted in about 25% more responses. Therefore, a second reminder may lead to a significantly higher response rate.

3) The third change we propose is to amend the wording of the help-seeking question asked at mid-point, post intervention and follow-up. This is so that we can collect more specific information about treatments received by participants. The question will be changed from:

"Have you visited a health professional (e.g. doctor, counsellor, psychologist) to help deal with your depression during the past [3 weeks] / [6 weeks] / [6 months]? (Yes/No)"

to:

"Which treatments for depression have you received from a professional during the past [3 weeks] / [6 weeks] / [6 months]? (multiple responses allowed)

• Nothing, just the consultation

• Psychological therapy

o Acceptance and commitment therapy

o Behaviour therapy

o Cognitive behaviour therapy

o Dialectical behaviour therapy

o Family therapy

o Mindfulness-based cognitive therapy

o Problem solving therapy

o Psychoanalytic psychotherapy

o Supportive psychotherapy or supportive counselling

o Not sure what type

• Medication

o Antidepressant medication (e.g. Zoloft, Lexapro)

o Antipsychotic medication (e.g. Zyprexa, Seroquel)

o Anti-anxiety medication (e.g. Valium, Xanax)

- o Mood stabilising medication (e.g. Lithicarb)
- o Stimulant medication (e.g. Ritalin, Modavigil)
- o Not sure what type

Jané-Llopis, E., C. Hosman, et al. (2003). "Predictors of efficacy in depression prevention programmes: Meta-analysis." *British Journal of Psychiatry* 183(5): 384-397.

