Participants will be recruited to the project website (<http://www.moodmemos.com>) by advertising on Google, links from depression and mental health websites and blogs, and posts on mental health forums. See Appendix A for a letter proforma asking whether webmasters would like to put a link to the moodmemos.com website on their website. An online screening questionnaire (Patient Health Questionnaire-PHQ9; Kroenke & Spitzer, 2002) will assess level of depressive symptoms and probable diagnosis of major depressive disorder. Participants who have sub-threshold depression symptoms will be provided with a plain language statement and invited to participate. They will be asked to complete a number of online questionnaires assessing psychological distress (K10; Kessler et al., 2002), functioning (Work and Social Adjustment Scale; Mundt et al., 2002) unpleasant experiences that may have caused depression (List of Threatening Experiences; Brugha et al., 1985), coping strategies, knowledge about depression, and sociodemographics (see Appendix B for all questionnaires), and to provide a name and email address. Those who meet admission criteria will be randomised to receive the active intervention or a control of educational information about depression. The intervention will be run on the internet and will be automated as much as possible through php computer scripts. The active group will receive email messages based on strategies thought to be effective and feasible by depression experts (Morgan & Jorm, 2009). See Appendix C for the text of each active message and an example of the layout of the email.

The control group will receive email messages based on information about depressive disorders, such as prevalence and risk factors. See Appendix D for the text of each control message and an example of the layout. The intervention will run for 6 weeks with emails sent twice a week. In addition to baseline, assessments will take place midway through the intervention, at the end of the intervention and 6 months after the end of the intervention. Total time commitment is estimated to be no more than 3 hours, including time to read each email as well as time taken to complete the four assessments.

Continuous outcomes (e.g. depressive symptoms) will be evaluated using mixed effects regression models, and dichotomous outcomes (e.g. presence of a depressive disorder) will be evaluated using logistic regression expressed as odds ratios with their 95% confidence intervals.

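### The phase-two inclusion list does not exclude people already randomised in phase one, so some phase-two controls may already have received the active emails

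*Protocol*

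**What the plan says.** The Request for Amendment, section 4.1, widens entry "to allow participation from anyone interested in the study regardless of their depression status". It removes the one exclusion that it discusses: "Undergoing concurrent treatment for depression will also not be an exclusion criterion". It then sets out the criteria under "To clarify, the inclusion criteria will now be", as items a to e: age 18 or older, internet access at least weekly, residence in one of six named countries, "Any score on the PHQ-9 depression questionnaire", and informed consent.

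On recruitment the same section says "We will continue to advertise the study and recruit participants in the same manner as before". Section 4.3 of the amendment states that the content of the intervention does not change. Phase one recruited 1336 people, and the phase-two target is 1600.

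Section 4.1 also plans to analyse the phase-two data separately from the data already collected in phase one, and adds: "This will also preclude any suggestion that the trial is being extended" in pursuit of significance.

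In the main application, section 2.2 draws phase one from adults in the same six countries. Section 1.3 asks participants "to provide a name and email address" and says that delivery is automated by scripts as far as possible. Section 5.3 describes the data as re-identifiable through a code.

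**The concern.** A phase-one participant who still lives in one of the six countries, still has weekly internet access and consents again meets all five criteria, whatever the current PHQ-9 score. Nothing shown asks about earlier participation or checks for a repeat sign-up. Advertising reaches the same kind of person as before.

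Such a person may have had the full set of active emails. If re-randomised to control, they bring that exposure into the control arm. If re-randomised to active, they receive the same messages a second time. Either way the difference between arms in these people may be smaller than in people new to the study. The amendment itself reports that preliminary phase-one analyses show the emails changing self-help coping behaviour, so carry-over is plausible.

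The same person could also contribute to both phases. The two sets of results would then not come from fully independent samples.

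**Working it through.** **Inputs from the documents** (Request for Amendment, section 4.1): 393 per condition for 80% power at 0.2 SD; pre-post correlation 0.5; about 50% non-completion at post-test; total 1600; 1336 recruited in phase one.

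**Assumptions, not in the documents:** two-sided alpha of 0.05; 1:1 allocation in both phases; returners complete at the same rate as others; the share *f* of phase two who are returners; the share *c* of the contrast lost in those previously on active emails.

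**Step 1. Reproduce the plan's figures.**
- n per arm = 2 × (1.96 + 0.8416)² / 0.2² = 392.4, so 393. A change-score analysis with correlation 0.5 has SD √(2 × (1 − 0.5)) = 1 and gives the same number.
- Allowing for attrition: 786 / 0.5 = 1572, which the plan rounds up to 1600.
- Completers per arm at 1600: 1600 × 0.5 / 2 = 400. Power = Φ(0.2 × √(400/2) − 1.96) = Φ(0.868) = 80.7%.

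The plan's figures stand, with a margin of only seven completers per arm.

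**Step 2. Dilution.** Half of the returners were on active emails in phase one. Their contrast is 0.2 × (1 − c), and everyone else's is 0.2. The average effect is therefore 0.2 × (1 − c × f/2). The number of randomised controls with earlier exposure is 1600 × f × ½ × ½ = 400f.

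**Step 3. Power at 400 completers per arm**, Φ(effect × √200 − 1.96), with c = 1:

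| Returners, f | People | As share of 1336 | Controls already exposed | Effect (SD) | Power |
|---|---|---|---|---|---|
| 0 | 0 | 0 | 0 | 0.200 | 80.7% |
| 1% | 16 | 1.2% | 4 | 0.199 | 80.4% |
| 5% | 80 | 6.0% | 20 | 0.195 | 78.7% |
| 10% | 160 | 12.0% | 40 | 0.190 | 76.6% |
| 20% | 320 | 24.0% | 80 | 0.180 | 72.1% |

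With c = 1, power drops below 80% at about 2% returners. With c = 0.5 the loss is smaller: 79.8% at 5% returners, 78.7% at 10% and 76.6% at 20%.

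**Step 4. Direction.** Returners are randomised afresh, so prior exposure is balanced between the phase-two arms in expectation. The estimate is pulled toward zero. The type I error rate within phase two is not inflated.

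**The case against.** Several points on the other side have force.

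- **The list may not be exhaustive.** Section 4.1(b) of the main application requires sufficient English, which is not among items a to e. A rule against repeat entry could therefore exist outside the list. The questionnaires, the amended plain language statement and the other attachments are not shown, and an operational duplicate check could sit there. This stands as a caveat. It does not change the fact that nothing visible excludes returners.
- **Returners are probably few.** In section 2.4 of the main application only advertising is ticked; the boxes for email and for people from an earlier study are blank. No payment is offered (section 2.6), and phase two is aimed at people who were previously ineligible. About half of phase one did not complete the post-test, so 320 returners would be nearly half of the roughly 668 who did. The 20% row is therefore an extreme, and low single figures are more plausible.
- **Power may be higher than planned.** If the model adjusts for baseline at correlation 0.5, the SD becomes √0.75 = 0.866 and only 295 per arm are needed. With 400 per arm, power is then about 90% at 0.20 SD and still about 84% at 0.18 SD. The document does not say that this adjustment is made.

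A reader might also infer that shared participants break the separation of the phases, or revive the charge of chasing significance. The text does not support this. The amendment promises only that newly collected data will be analysed apart from phase-one data. It does not promise different people, and no pooling is planned. Attenuation toward zero makes a significant result harder to reach. Nor does the list admit every phase-one participant: current residence, internet access and fresh consent are still required.

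**Conclusion.** The gap in eligibility is real. As written, the phase-two criteria let people randomised in phase one enter again, and some phase-two controls may already have had the active emails. This belongs to the protocol, because an analysis plan cannot undo an admission and a second randomisation.

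The harm is conditional and conservative in direction: possible attenuation and some lost power. It is negligible at 1% returners (80.4% against 80.7%) and amounts to about 2 percentage points at 5% and 4 at 10%, if all contrast is lost in prior active recipients and the analysis is the unadjusted or change-score one that matches 393 per arm. The true share of returners cannot be derived from the documents. Overlap would leave the phases less than fully independent as samples, which matters if their results are read as two separate pieces of evidence, but the promised separate analyses remain possible.

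**What to change.** 1. Add to the phase-two criteria: *not previously randomised in this study (phase one or phase two)*.
2. Enforce it before allocation with a screening question on earlier participation and an automatic match of the registration name and email address against the stored records of both phases. The question helps to catch people who return with a new address.
3. If a returner is found after allocation, run the phase-two analysis with and without that person. Identify returners only from pre-randomisation information, so that outcomes play no part.

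The cost is one line in the criteria, one screening question and one lookup in the existing scripts, since names and email addresses are already collected. A few willing repeat participants are lost.

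### The only added step to retrieve the roughly 50% missing outcomes is a second reminder at post-test and follow-up; raising the target to 1600 protects power but not against non-response bias, and no short depression-scale reply or mid-point reminder is described

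*Protocol*

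**What the plan says.** The Request for Amendment, section 4.1, reports that about half of phase-one participants did not complete the post-test and that non-completion of assessments reached 50%. It responds in two ways.

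- **More recruitment.** It states that "a sample of 393 per condition would give 80% power" at 0.2 SD, assumes a pre-post correlation of 0.5, and sets the target at 1600 so that similar attrition still leaves that number.
- **One more request.** The second change is to "send an additional reminder email requesting the participant to complete post- and follow-up assessments, bringing the number of reminders to two". The reason given is that the first reminder brought in about 25% more responses.

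The Protocol's Method (section 1.3) says that, after baseline, "assessments will take place midway through the intervention, at the end of the intervention and 6 months after the end of the intervention". The third change in the amendment also treats the mid-point as a live assessment, because the reworded help-seeking question is asked there too. That change replaces one Yes/No item with a multi-response list of therapies and medicines. On analysis, section 1.3 says: "Continuous outcomes (e.g. depressive symptoms) will be evaluated using mixed effects regression models".

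The visible text describes no shortened reply for people who have not answered, and no extra reminder at the mid-point.

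**The concern.** With half the outcomes missing, the symptom comparison depends on an assumption about the people who are not seen. More recruitment shrinks the standard error of the estimate among responders. It does not move that estimate towards the effect among everyone randomised. Only outcome data from would-be non-responders can do that.

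The second reminder is the one new measure aimed at those people, and it leaves two inexpensive options unused. Someone who has passed over earlier requests is, on the visible text, asked for the assessment again rather than for the depression scale alone, while the same amendment lengthens one item. The extra reminder also names two of the three post-baseline assessments. For a person who misses both the post-test and the follow-up, a mid-point symptom score would be the only post-randomisation value. The planned mixed model would use it, and it would make a missing-at-random assumption easier to defend.

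Section 3.5 of the application argues that a non-significant result could still rule out this approach as effective. That argument holds only if the people who answer represent those randomised.

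**Working it through.** **1. The plan's own figure.** Inputs from Request for Amendment 4.1: 0.2 SD, 80% power, equal arms. Alpha is not stated; two-sided 5% is assumed.

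n per arm = 2 × (1.960 + 0.842)² / 0.2² = 2 × 7.849 / 0.04 = 392.4, so 393. This reproduces.

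Inflation for 50% loss: 2 × 393 / 0.5 = 1572, against 1600 stated. This is consistent. At 1600, completers are 1600 × 0.5 / 2 = 400 per arm, with 80.7% power for an unadjusted comparison (normal approximation).

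**2. Power under the kind of analysis planned.** With baseline correlation 0.5, the residual variance is 1 − 0.5² = 0.75. The variance of the post-test contrast is 2 × 0.75 / 400 = 0.003750, so SE = 0.0612. Then 0.2 / 0.0612 − 1.96 = 1.31, which is about 90.4% power. Power is not the weak point.

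**3. What the planned second reminder may already achieve.** The base of the 25% is not defined, so three readings are shown. Each assumes that 50% completion was reached after one reminder, and that the second reminder has the same yield among remaining non-responders as the first.

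| Reading of 25% | Completion before first reminder | Yield among non-responders | Completion after second | Completers of 1600 | Unadjusted power |
|---|---|---|---|---|---|
| Relative increase | 0.5 / 1.25 = 40% | 0.10 / 0.60 = 16.7% | 58.3% | 933 | 86% |
| 25% of non-responders | (0.5 − 0.25) / 0.75 = 33.3% | 25% | 62.5% | 1000 | 89% |
| 25 percentage points | 25% | 0.25 / 0.75 = 33.3% | 66.7% | 1067 | 90% |

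The benefit of a short reply is the difference between a short and a full second reminder. The documents give no figure for that.

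**4. Why sample size does not answer the bias question.** Let m be the share missing, and g the effect in responders minus the effect in non-responders. The responder estimate then differs from the effect in all randomised people by m × g, and N does not appear. For an assumed g of 0.1 or 0.2 SD, held fixed:

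| Missing share | g = 0.1 | g = 0.2 |
|---|---|---|
| 50% | 0.050 | 0.100 |
| 41.7% | 0.042 | 0.083 |
| 37.5% | 0.038 | 0.075 |
| 33.3% | 0.033 | 0.067 |

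For example, 0.2 SD in responders and zero in non-responders is 0.5 × 0.2 = 0.1 SD overall at 50% missing. These values of g are illustrations, not estimates.

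**5. What mid-point scores would add to precision.** Assumed: correlations 0.5 baseline-mid and 0.7 mid-post, and mid-point seen in 90% of post-test responders. From the amendment: 0.5 baseline-post. Given baseline, the mid-post correlation is (0.7 − 0.25) / 0.75 = 0.6, and its square is 0.36. If k of the 400 per arm without a post-test supply a mid-point score, the variance is roughly 0.003750 × [1 − 0.36 × k / (400 + k)]. The table uses the 90% assumption, which differs only slightly from this formula.

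| Mid-point response among post-test missing | Variance | Information gained | Power at 0.2 SD |
|---|---|---|---|
| 0% | 0.003750 | – | 90.4% |
| 10% | 0.003628 | 3.4% | 91.3% |
| 20% | 0.003528 | 6.3% | – |
| 30% | 0.003443 | 8.9% | 92.6% |

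The precision gain is small. The case for mid-point data rests on bias.

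**The case against.** A reader might infer that the second reminder is the plan's only answer to attrition. It is not. The target is raised to 1600 for this reason, and mixed models use partial follow-up. A reader might also infer that the trial is short of power. Steps 1 and 2 show otherwise, and any power gain credited to a short reply would have to exclude what the already planned second reminder brings in. A third inference, that recoverable data are being lost, also goes beyond the text: no yield is given for a shorter reply, and response at the mid-point is not reported.

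Several premises cannot be checked, because the questionnaires are in Appendix B, which is not shown. Section 1.3 names the PHQ-9 as the screening questionnaire and lists the other scales for people being invited; it does not say which are repeated later. The only item the visible text places at the mid-point is the help-seeking question. Item order, saving of partial pages and any existing mid-point reminder are unknown, so part of the remedy may already be in place.

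There is also a trade-off. A short final request could draw some people who would have given a full assessment, at the cost of coping, functioning and treatment data. Coping is where the amendment reports the clearer phase-one effect.

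All of this stands as a limit on the point. It does not remove the core: the one new retrieval step names two of three post-baseline assessments and has no short form, and a larger N cannot compensate for informative non-response.

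**Conclusion.** The point holds as a low-cost improvement to a retention rule that the amendment itself sets. It is not a contradiction or a miscalculation. The stated 393 per arm and the 1600 target reproduce, and power is adequate: about 81% unadjusted and about 90% with baseline adjustment at correlation 0.5, for 400 completers per arm and two-sided 5%.

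What remains open is bias from up to half the outcomes being missing. It scales with the missing share and with how far non-responders differ, and not with N. The documents do not allow the benefit of a short reply or a mid-point reminder to be sized. The conclusion assumes that a depression scale is collected at the mid-point, post-test and follow-up, and that no short reply or mid-point reminder exists in material not shown.

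**What to change.** Amend the second change for phase two, identically in both arms:

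1. Make the second (final) reminder link to a page where the depression outcome scale comes first and is saved on submission. This is the PHQ-9 if that is the follow-up measure. Offer the remaining questionnaires straight afterwards as optional.
2. Apply the same reminder schedule to the mid-point assessment, if it does not already have one.

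The cost is a change to the automated scripts and the reminder text, with no extra recruitment. Some late responders may give a depression score without the coping, functioning or treatment items; placing those items directly after the saved scale limits that loss. Non-responders will receive extra emails at the mid-point.
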